## **D. DESIGN AND METHODS**

### **D.1. Summary**

This clinical trial aims to assess the effects on the risk of major cardiovascular events of two intensive behavioral counseling and nutrition education interventions in comparison with a low-fat control group for a median duration of 6 years. Both intervention groups are assigned a traditional MeDiet. In one of these two groups we supplement the diet with EVOO (1 liter/week) and the other with 30 g/d of mixed nuts (15 g walnuts, 7.5 g hazelnuts, and 7.5 g almonds). The third arm of randomization is the control group, where participants do not receive education on the MeDiet, but are given advice on how to follow a low-fat diet. We are recruiting men (age: 55 to 80 years) and women (age: 60 to 80 years) with either diabetes or three or more major cardiovascular risk factors. All participants are free of cardiovascular disease at baseline. Study participants are randomized to three equally sized groups (2,350 in each). They will be followed-up for clinical outcomes during a median time longer than 5 years by the primary care physicians who recruited them for the study. The primary endpoint will be a composite outcome of cardiovascular events (cardiovascular death, myocardial infarction, and stroke).

## **D.2. Design**

Parallel group, multi-center, single-blind, randomized trial aimed at assessing the effects on the incidence of major cardiovascular events of intensive behavioral counseling and nutrition education interventions based on the MeDiet in comparison with a similar intervention aimed at decreasing the total fat content of the diet. The Institutional Review Board (IRB) of the Hospital Clinic (Barcelona, Spain) accredited by the US Department of Health and Human Services (DHHS) update for Federalwide Assurance for the Protection of Human Subjects for International (Non-US) Institutions # 00000738 approved the study protocol on July, 16, 2002. This trial has been registered in the Current Controlled Trials register at London with the ISRCTN number 35739639 (<http://www.controlled-trials.com/ISRCTN35739639>)

Controlled feeding studies are the best procedure to assess the biological effect of nutrients on intermediate markers of cardiovascular risk. However, the existence of multiple pathways for the effects of dietary exposures on CHD, some of them newly identified and others likely to be identified in the next years, reinforces the need to study clinical outcomes. If clinical outcomes are to be observed, a controlled feeding design is completely unfeasible. From a public health perspective, a behavioral intervention coupled with an easy (free) access to representative healthy foods is a more realistic test of the effectiveness to be attained with official policies and health promotion activities in public health.

The principal aim of the study is to compare the effects of two food patterns, the MeDiet and a low-fat control diet, on the primary prevention of cardiovascular diseases. The rationale for using 2 MeDiet groups (one with supplemental EVOO and one with supplemental nuts) instead of one is as follows. Besides being a rich source of MUFA, EVOO used in one arm of the study is a good source of phenolic antioxidants. One-half the dose of the nuts used in another arm of the study is made up of walnuts, thus containing sizeable amounts of PUFA, especially  $\alpha$ -linolenic acid, the plant-derived omega-3 fatty acid. Thus, one MeDiet is enriched in MUFA and phenolic antioxidants and the other MeDiet is supplemented with both n-6 and n-3 PUFA. Although having the same general food pattern of the MeDiet, the two arms of the study differ in the intake of two foods (EVOO and nuts) and two nutrients (phenolics and PUFA) that are all felt to be important in cardiovascular prevention and may have differential beneficial effects. Therefore we chose a 3-group randomization design with the general aim of comparing two food patterns, the MeDiet and a low-fat diet, for cardiovascular outcomes, considering that the single foods supplemented in each MeDiet may individually contribute to the effects of the overall MeDiet food pattern. The rationale for the free provision of individual food items (olive oil or tree nuts) is that they may contribute to a higher compliance with the overall MeDiet food pattern. However, because of the high fat load of both EVOO and nuts, we felt that it was unfeasible to supplement the two foods together in a single MeDiet group of participants.

## **D.3. Outcomes**

- Primary outcome: composite endpoint of cardiovascular death, non-fatal myocardial infarction, and non-fatal stroke.
- Secondary outcomes: death of any cause and incidence of angina leading to a revascularization procedure, heart failure, diabetes mellitus, cancer, dementia, and other degenerative disorders.

- Other outcomes: changes in blood pressure, body weight, adiposity measures, blood sugar, lipid profile, markers of inflammation, and other intermediate markers of cardiovascular risk (see also section D.11.5)

#### **D.4. Sample size**

A sample size of  $n=6,999$  with randomization to 3 equally sized groups (two intervention groups and one control group, 2,333 patients each) will provide sufficient statistical power to evaluate the effect of the Mediterranean food pattern on the primary outcome (fatal or non-fatal myocardial infarction and fatal or non-fatal stroke). The sample size estimates were computed by comparing two binomial proportions representing the event rates in one of the treatment groups and in the control group. We assumed an 80% power ( $1-\beta=0.8$ ) and ( $1-\alpha/2=0.975$ ) for a 2-sided p-value of 0.05. To estimate the projected cumulative incidence in the control group, we used the number of events observed in the first year follow-up (rate of 1.3%). Adapting this figure to a 6-year follow-up and taking into account the aging of our study population during follow-up, an 11% average absolute risk can be assumed for the control group. The minimum relative decrease in number of events in the intervention groups should be 25%. Then,  $p_1 = 0.11$  and  $p_2 = (0.117)(0.75) = 0.0825$ . With these assumptions, the total number of participants required is 1,877 per group. We plan to include 2,333 subjects in each group to allow for 10% losses during follow-up and also for a lower incidence than expected.

#### **D.5. Timeline, progress and funding.**

The Spanish Ministry of Health - Instituto de Salud Carlos III (ISCIII) funded the current project for the period 2003-2005 (RTIC G03/140) and a thematic network of 16 Spanish research groups was established. In 2006 a new funding modality was established by ISCIII through the CIBER\_Fisiopatología de la Obesidad y Nutrición (CiberOBN), which provided reasonable funding for one-half of the original research groups, while the other half were funded by a new research network (RTIC RD 06/0045). Other official funds from Spanish government agencies have been obtained for funding subprojects related with intermediate outcomes (lipoproteins, inflammatory markers, genomic and proteomic studies, etc.). Additional funds are obtained from other sources for the overall project, limited to small donations from Food Companies in cash and other commodities, i.e., printing of intervention material, such as recipes. Obviously, the donation by Food Companies of all the EVOO and mixed nuts needed throughout the duration of the study is a substantial contribution,

##### **D.5.1. Planning**

The needed personnel (a minimum of a dietitian and a nurse for each of the 11 field centers - FC) were trained and certified in nutritional education and procedures for extraction and storage of blood and other biological samples, respectively, at the beginning of the study. From March to September 2003 we developed the logistics, protocols, operations' manual, and instruments, forms, and data entry/management systems. Each FC contacted approximately 20 Primary Care Centers (PCC) to recruit participants. During this same period, menus and buying lists of Mediterranean products to be provided to participants were developed.

#### D.5.2. Pilot study

The recruitment for the pilot phase of the study started between October and November 2003. After 3 months, 772 participants were assessed for compliance with dietary advice and changes in intermediate biological markers of cardiovascular risk (see section C.3).

#### D.5.3. Implementation

After obtaining reassuring data confirming adequate changes in diet and risk factors during the pilot phase, recruitment went on and was finished on 31 March 2009 with a total of 7350 participants. The FC have recruited from 350 to 1000 participants, referred by approximately 20 primary care physicians for each FC.

#### D.5.4. Follow-up

Participants recruited in 2003 will be followed for up to 8+ years and will have the longest follow-up. Participants entering the study during the year 2008 will be followed only for 3-4 years, thus having the shortest follow-up. Consequently, we expect a median follow-up of 6 years.

#### D.5.5. Analysis/closeout

Trial closeout will take place by December 31, 2011. During early 2012, the ascertainment of outcomes, laboratory measurements, data entry, and respond-to-data edits will be completed, and data will be prepared for statistical analysis. Writing of the reports for scientific publications will be done during late 2012.

### D.6. Study population / eligibility criteria

Trial participants consist of nearly 7,000 community-dwelling high-risk persons ( $\approx 700$  in each FC), with ages 55 to 80 years for men and 60 to 80 years for women. They should be free of cardiovascular disease and meet at least one of two criteria.

D.6.1 Inclusion criteria: either **a)** or **b)** should be met.

- a) Type 2 diabetes.** Diagnosis of diabetes is based on at least one of the following criteria: i) Current treatment with insulin or oral hypoglycemic drugs; ii) Fasting blood glucose  $> 126$  mg/dl (fasting is defined as no caloric intake for at least 8 hours); iii) Casual blood glucose  $> 200$  mg/dl with polyuria, polydipsia, or unexplained weight loss; iv) Blood glucose  $> 200$  mg/dl in two measurements after an oral glucose tolerance test. **OR**
- b) Three or more** of the following **risk factors:** i) Current smoker ( $>1$  cig/day during the last month); ii) Hypertension (systolic BP  $\geq 140$  mm Hg or diastolic BP  $\geq 90$  mm Hg or antihypertensive medication); iii) LDL-cholesterol  $\geq 160$  mg/dl; iv) HDL-cholesterol  $\leq 40$  mg/dl in men or  $\leq 50$  mg/dl in women, independently of lipid-lowering therapy; v) Body mass index  $\geq 25$  kg/m^2; vi) Family history of premature CHD (definite myocardial infarction or sudden death before 55 years in male 1st-degree relatives or before 65 years in female 1st-degree relatives).

D.6.2. Exclusion criteria. Major exclusion criteria are: i) Documented history of previous cardio-vascular disease, including CHD (angina, myocardial infarction, coronary revascularization procedures or existence of abnormal Q waves in the electrocardiogram (EKG)), stroke (either ischemic or hemorrhagic, including transient ischemic attacks), and

symptomatic peripheral artery disease diagnosed with vascular imaging techniques; ii) Severe medical condition that may impair the ability of the person to participate in a nutrition intervention study; iii) Any other medical condition thought to limit survival to less than 1 year; iv) Immunodeficiency or HIV-positive status; v) Illegal drug use or chronic alcoholism or total daily alcohol intake >50 g/d; vi) Body mass index > 40 kg/m^2; vii) Difficulties or major inconvenience to change dietary habits; viii) Impossibility to follow a Mediterranean-type diet for religious reasons or due to the presence of disorders of chewing or swallowing; ix) A low predicted likelihood to change dietary habits according to the Prochaska and DiClemente stages of change model (Nigg, 1999); x) History of food allergy with hypersensitivity to any of the components of olive oil or nuts; xi) Participation in any drug trial or use of any investigational drug within the last year; xii) Institutionalized patients for chronic care, those who lack autonomy, are unable to walk, lack a stable address, or are unable to attend 3-monthly visits at their FC; xiii) Illiteracy; and xiv) Patients with an acute infection or inflammation (i.e., pneumonia) are allowed to participate in the study 3 months after resolution of their condition.

#### **D.7. Recruitment**

Most FC has considerable experience and a successful track record of recruiting participants for both epidemiological studies and clinical trials. The participation of primary care physicians has ensured a high enrollment rate. Because these physicians are responsible for the usual medical care of participants and they are aware of their risk factors, no potential ethical conflict regarding confidentiality existed at the stage of identification of suitable participants for the trial. This process started by extracting their names from the records of the Primary Care Center (PCC). Most PCC (over 70 %) participating in the study have computer-based records of patients, making the selection relatively simple. The clinical records of these persons were then individually reviewed to exclude those who did not meet eligibility criteria. Candidates were contacted by telephone and invited to attend a visit in the PCC, where the purpose and characteristics of the study were explained and a signed informed consent was obtained (see below). A brief general explanation of the study, including the possibility that they might receive free allowances of olive oil or nuts for the duration of the trial, was given in this first visit. Our experience has been that >70 % of candidates approached in this way agreed to return for the screening visit.

#### **D.8. Participants' visits**

Participants' eligibility for the trial was determined by review of clinical records and by two formal screening visits. In these visits, questionnaires were filled in, a clinical history was taken, anthropometric and BP measurements were made, and fasting blood for biochemical analyses was obtained. Information collected in the screening visits will also provide baseline data for subsequent analyses of the effects of the interventions on intermediary biomarkers and risk factors.

- **Pre-Screening Evaluation:** After review of clinical records, eligible candidates were contacted by telephone to know if they were both capable and willing to participate in the study. Those giving a positive response were scheduled for the first visit. Data on participation proportion (recruited:eligible ratio), collected in all field centers has been between 0.75 and 0.90.

- **Screening visit 1:** The visit, performed by the PCP, served to identify inclusion/exclusion criteria in a more comprehensive manner. This 15-30 minute visit included: a) A face-to-face administration of a 26-item questionnaire to inquire about the medical conditions and risk factors related to eligibility, including assessment of the willingness to make diet changes (Prochaska model). b) A review of the last EKG if available in the clinical record. If no EKG had been performed within the last year, an EKG was performed during this visit. c) If the candidate met all the requirements (including EKG\_data), an informed consent form was given to him/her to be signed after a detailed explanation of all procedures and of the anticipated time commitment (see <http://www.predimed.org>). The informed consent comprised two parts, one for trial participation and biochemical analyses and another for DNA collection for genetic analyses. d) The following forms and questionnaires to be completed at home were provided (see <http://www.predimed.org>):

- A detailed written explanation of the study.
- A food frequency questionnaire (FFQ) with 137 items plus vitamin/minerals supplements (adapted from the Willett questionnaire and validated in Spain, see **Martin-Moreno, 1993**) plus specific questions for patterns of alcohol consumption.
- The Minnesota physical activity questionnaire (validated Spanish version, **Elosua, 1994 & 2000**).

e) The participant was instructed to collect toenail specimens and bring them in the next visit.

f) The next screening visit (2) was scheduled and the candidate was told to attend it after an overnight fast for blood extraction.

After the first screening visit, the participant was randomized to one of three diet groups.

- **Randomization:** The study nurse randomly assigned each participant to the corresponding intervention group following tables of random allocation according to the recruitment order. These tables were centrally elaborated by the Coordinating Unit and provided a stratified random sequence of allocation for each FC. The four strata for stratified randomization were built according to gender and age (cut-off point: 70 years). The study nurses were independent of the nurse staff of the PCC. Therefore, they were not involved in the usual clinical care of participants and their exclusive role was to collect data for the PREDIMED trial.

- **Screening visit 2:** This 1-hour visit included the following: a) A simplified 14-item questionnaire for assessment of adherence to the MeDiet (see <http://www.predimed.org> and **Martinez-Gonzalez, 2004c**). b) In a face-to-face interview with the candidate, the dietitian explained again in detail the purpose and development of the study. c) The dietitian reviewed (and completed with the candidate if needed) the FFQ and physical activity questionnaires. Alternatively, she helped the candidate who had difficulties at home to fill in the questionnaires during the visit. d) The nurse measured the weight, height, waist circumference, and BP. e) The nurse performed a venipuncture, obtained and handled blood samples, and proceeded to prepare the specified serum, plasma, and buffy-coat aliquots. f) A urine sample and toenail specimens were also collected by the nurse. g) A 47-item general questionnaire collecting information about current medication and risk factors was filled-in. Information to fill this questionnaire was also abstracted from clinical records by the research nurse.

- **Follow-up visits:** Further clinical evaluations (outside of the intervention) are limited to yearly follow-up visits, which include the same examinations performed at the baseline visit, with exception of the general questionnaire, which is substituted by a follow-up

questionnaire, and a tolerance / adverse events questionnaire (see <http://www.predimed.org>). Blood and urine samples are collected at baseline and years 1, 3, 5 and 6 (or final visit). Primary and secondary outcomes are evaluated at each follow-up visit.

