- f)** The next visit (screening visit 2) is scheduled and the candidate is told to attend it after an overnight fast for blood extraction.

After the first screening visit, the participant is randomized to one of three diet groups.

- **Randomization:** The study nurse randomly assigns each participant to the corresponding intervention group following tables of random allocation according to the recruitment order in blocks of 50 participants, balanced by sex and age group (< 70 years and  $\geq$  70 years). These tables have been centrally elaborated by the Coordinating Unit and provide a stratified random sequence of allocation for each FC using closed envelopes. The four strata for stratified randomization are built according to gender and age (cut-off point: 70 years). The Primary Care physicians do not participate in the process of randomization. The study nurses are independent of the nurse staff of the PCC. Therefore, they are not involved in the usual clinical care of participants, their first and exclusive role being to collect the data for the PREDIMED trial.

- **Screening visit 2:** This 1 hour visit includes the following:

**a)** A simplified assessment of adherence to the MeDiet (14-item questionnaire). **b)** In a face-to-face interview with the candidate, the dietitian explains again in detail the purpose and development of the study. **c)** The dietitian reviews (and completes with the candidate if needed) the FFQ and physical activity questionnaires. Alternatively, she helps the candidate who had difficulties at home to fill in the questionnaires during the visit. **d)** The nurse measures the weight, height, waist circumference, and BP, and performs a measurement of the ankle-brachial blood pressure index. **e)** The nurse performs a venipuncture, obtains and handles blood samples, and proceeds to prepare the specified serum, plasma, and buffy-coat aliquots. **f)** A urine sample and toe nail specimens are collected by the nurse. **g)** A 47-item general questionnaire collecting information about current medication and risk factors is filled-in. Information to fill this questionnaire is also abstracted from clinical records by the research nurse.

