#### D.12. Statistical Analyses

The analyses will be based on the intention-to treat principle. With the actual sample size, it is assumed that we will have enough statistical power to evaluate the effects of the MeDiet (the two MeDiet groups considered as a single one) compared to the Low-fat Control diet on the primary prevention of cardiovascular diseases. We also might be able to assess differences in outcomes for the two MeDiets if the specific supplements of EVOO and mixed nuts prove to be differentially cardioprotective. The main variable for analysis will be time from randomization to event. For a given outcome, the time of the event will be defined as the number of days from randomization to the first post-randomization diagnosis, as determined by the adjudicator. For silent MI, the date of the follow-up EKG will be applied. Participants without a diagnosis will be censored at the time of last follow-up contact. The generally accepted method for analyzing this type of data is the log rank statistic. It has the advantage of requiring no assumptions other than the random assignment of the intervention. This analysis will be the primary measure of the success or failure of the trial. However, if baseline imbalances between groups are observed for any of the main CHD risk factors, a Cox proportional hazard analysis will be conducted stratified by FC, age, sex and adjusted for major risk factors. Primary outcome comparisons will be estimated as hazard ratios. Adjustment for other relevant variables (body mass index, physical activity, education level, marital status) also will be applied.

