#### D.13. Monitoring Plan

The Data and Knowledge Management Center (DKMC) will be responsible for preparing reports to monitor the progress of the study for the Steering Committee and the Data and Safety Monitoring Board (DSMB). These reports will focus on a) general progress of candidate recruitment and person-year of follow-up in comparison to pre-established targets; b) participant adherence (biochemical markers and FFQ data of compliance and comparison with targets for nutrients and food groups); c) quality control (digit preference, variability, outliers); d) clinical outcome data at each center and primary and secondary endpoints (group comparisons with respect to both the primary outcome, total mortality, and other secondary outcomes). In these sections, data will be provided for the study as a whole and, where appropriate, separately for each FC. Reports will be

mailed to members of the DSMB two weeks prior to the meeting or to the date of review. Steps will be taken to insure security and confidentiality, including distribution by certified mail and enactment of a return policy of all reports. Comparison of groups with respect to major outcomes will be updated two days before the meeting so that the DSMB will have the most up-to-date data possible.

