#### D.13.1. Quality of Data

To assess the reliability of the data included in the questionnaires and databases, external personnel will review medical records of a random sample of the participants. Data of around 25% of the participants included in each FC will be evaluated. Then DKMC and Data and Knowledge Management Center (DKMC) members will confirm these data (See later).

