|                               | Zaragoza University                                | SLU-5                                                                                                                                                      |
|                               | Barcelona University – Pharmacy School             | SLU-6                                                                                                                                                      |

\*CSIC: Superior Council for Scientific Research. IMIM: Municipal Institute for Medical Research.

A private web-based system of data access has been created ([www.predimed.org](http://www.predimed.org)), where authorized investigators can download all the forms, datasets and published papers.

For privacy and security, an ID and password are required to access the data and the forms. This web-based system is used to send data to the Data Manager. Quality control reports will be generated for key aspects of the trial, i.e., digit preference and variability. To reduce data entry expenses and speed processing, the questionnaires and data forms are optically scannable. The data forms will be entered in duplicate and missing data checks will be performed. After data entry, cross-form edit checks will also be performed. Data inconsistencies will be checked. Audits will be rerun periodically to detect unsolved problems. Standardized edit reports that summarize problems in the database provide an additional method of assuring data quality. To minimize the potential for error, we have developed a detailed Manual of Operations. In addition we will conduct annual training meetings for staff. The DKMC will monitor the performance of each FC and will recommend new or corrective procedures in case deficiencies are noted. Until the end of the trial, all FC will be masked to trial outcome data, with the exception of the statisticians, the Data Manager and the external DSMB. Due to the nature of the intervention, however, dietitians and nurses at each FC need to be unmasked to diet assignment. The Clinical Event Subcommittee will be blinded to participants' allocation.

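### The current protocol describes no concealment of the centre allocation tables and no check of recorded arms against them, although the primary log-rank test relies on random assignment

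*Supplement*

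**What the plan says.** **Allocation.** Section D.8 of the May 2009 protocol states: "The study nurse randomly assigned each participant to the corresponding intervention group following tables of random allocation according to the recruitment order". On the source of the tables it adds: "These tables were centrally elaborated by the Coordinating Unit and provided a stratified random sequence of allocation for each FC". The strata are sex and age, cut at 70 years. The section does not say how the next assignment was kept from the person making it. Version 1 (October 2003, section D.5) did; its tables were to "provide a stratified random sequence of allocation for each FC using closed envelopes". None of the listed amendments mentions a change to this.

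**Who assigns.** The study nurses also collect the trial data. Section D.15 says that "dietitians and nurses at each FC need to be unmasked to diet assignment".

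**Checks.** Section D.13.1 says "external personnel will review medical records of a random sample of the participants", covering about 25% of each FC, to test the reliability of questionnaires and databases. In the D.13 monitoring reports, quality control means digit preference, variability and outliers. Section D.15 adds edit checks, audits and a general commitment: "The DKMC will monitor the performance of each FC and will recommend new or corrective procedures in case deficiencies are noted".

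**Analysis.** Section D.12 makes an intention-to-treat log-rank test the measure of success. Of that test it says: "It has the advantage of requiring no assumptions other than the random assignment of the intervention". A Cox model stratified by FC, age and sex and adjusted for major risk factors follows only if a main coronary risk factor is seen to be imbalanced between groups.

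**The concern.** D.12 names the one assumption that the primary test needs, and no stated procedure verifies it. If assignments at a centre did not follow its table, the arms there would not be comparable. Analysing participants as assigned does not cure that, because the assignment itself would be the source of bias. The log-rank test would count the centre as properly randomised, and so would the interim looks in D.13.2.

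Bias in favour of the Mediterranean diets would raise the chance of a false claim of benefit. Bias the other way would hide a real one. If households or clinics had been assigned as units, the usual variance would also be too small. Nothing in D.6 bars relatives, D.10.2 sizes the food supplies for families, and each FC approached about 20 primary care centres (D.5.1). A check should therefore look for this as well.

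Recruitment closed on 31 March 2009 (D.5.3), so allocation cannot be redesigned. Verification and the analysis response remain open until closeout at the end of 2011 (D.5.5).

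**Working it through.** **1. Does any stated check reach the allocation?**

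| Safeguard | Compares | Reaches the allocation table? |
|---|---|---|
| D.13.1 external review, about 25% per FC | Questionnaires and databases with medical records | No; the purpose is data reliability |
| D.13 reports | Recruitment, adherence, measurement quality, outcomes | No |
| D.15 edit checks, audits, FC performance | Form against form; general performance | Not stated |
| D.12 Cox model | Baseline risk factors between arms, trial-wide | Indirectly, and only if an imbalance is seen |

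The last row is weak for a problem at one centre. The largest centre holds 1,000/7,350 = 13.6% of participants. A 10-point difference in the prevalence of a risk factor there (assumed) would appear trial-wide as 10 x 0.136 = 1.4 points.

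**2. The plan's own figure.** D.4 assumes 11% against 8.25%, 80% power and two-sided 0.05. The two-proportion formula gives 1,805 per group, and 1,877 with a continuity correction. The stated 1,877 reproduces exactly, so this point does not touch the sample size.

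**3. Possible size (illustration).** From the documents: 7,350 enrolled, centres of 350 to 1,000 (D.5.3), 11% control risk and 10% losses (D.4). Assumed: no true effect, one affected centre, and controls there at 20-50% higher risk than the diet arms.

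- Centre share s: 350/7,350 = 0.0476 to 1,000/7,350 = 0.1361.
- Apparent HR = 1/(1 + s x excess).
- Followed per arm: 7,350 x 0.9/3 = 2,205. Control events e1 = 0.11 x 2,205 = 242.6; diet-arm events e2 = HR x e1.
- Shift = -ln(HR)/sqrt(1/e1 + 1/e2).
- Type I error = Φ(-1.96 + shift) + Φ(-1.96 - shift).

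| Centre | Excess | HR | Shift | Type I error |
|---|---|---|---|---|
| 350 | 20% | 0.991 | 0.104 | 5.1% |
| 350 | 50% | 0.977 | 0.258 | 5.8% |
| 1,000 | 20% | 0.974 | 0.294 | 6.0% |
| 1,000 | 50% | 0.936 | 0.713 | 11.0% |

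With the planned 2,333 per group (about 2,100 followed, 231 control events) the last figure is 10.7%.

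**4. Another parameterisation.** Assume an apparent HR of 0.7 inside a centre of 1,000. The overall ln HR is 0.1361 x ln 0.7 = -0.0485, so HR = 0.953. The type I error is 8.3% for one diet arm against control and 9.5% for both diet arms pooled. An apparent HR of 0.5 there would give 18.0% and 22.4%. The result follows the assumption.

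**5. Clustering (illustration).** About 20 clinics per FC gives 17.5 to 50 participants per clinic. At an assumed intraclass correlation of 0.01, the design effect 1 + (m - 1) x 0.01 is 1.17 to 1.49 within a centre that assigned by clinic.

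**6. Can the trial afford to drop a centre?**

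- Without a centre of 350: (7,350 - 350) x 0.9/3 = 2,100 per arm, pairwise power 85.6%.
- Without a centre of 1,000: 1,905 per arm, 82.1%, still above 1,877.
- Without two centres of 1,000: 1,605 per arm, 75.2% pairwise, or 86.7% with the diet arms pooled.

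**The case against.** The case against has real weight.

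- **A reader might infer that the tables lay open and the nurse could see the next assignment.** The documents do not say so. Version 1, dated when recruitment began, specified closed envelopes. The 2009 text is a shorter, past-tense account written after recruitment closed. Silence supports only the statement that no concealment is described.
- **A reader might infer that some centre did depart from its table.** No document shows or suggests this. The household and clinic scenarios only say what a check should look for.
- **Roles are partly separated.** A primary care physician conducts the first screening visit and obtains consent before randomisation, the nurses are independent of clinic staff, and a blinded committee judges outcomes. This narrows the route for steering enrolment. It does not verify the order in which consented people were matched to the table. That nurses know the diet follows from the intervention and says nothing about allocation.
- **Strong selection could show at baseline and trigger the Cox model.** It could, but a single centre is diluted in a trial-wide comparison. Weight, blood pressure and blood samples are taken at the second screening visit, after randomisation. Adjustment for measured factors does not restore randomisation.
- **A check may exist elsewhere.** The Manual of Operations is not shown, and the contents page lists a statistical analysis plan whose text was not available here. The point is therefore confined to what the protocol states.
- **The magnitude is assumed.** This stands: at the low end the effect is negligible.

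**Conclusion.** The point holds as a gap in verification. The current protocol describes neither concealment of the FC tables nor a comparison of recorded arms with them, and the conditional Cox model is not a substitute. A departure at one centre could pass unnoticed into an analysis whose validity depends on there being none.

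The documents give no evidence of a departure and do not support a claim that the randomisation failed. The figures (HR 0.99 to 0.94; type I error about 5.1% to 11% for one pairwise comparison) rest on an assumed 20-50% excess risk among controls at a single centre, an assumed direction and no adjustment. They show that the matter can range from trivial to material; they do not estimate what happened. The change is recommended because it is cheap and protects the assumption behind the primary result.

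**What to change.** 1. **D.13.1.** Before database lock and masked to outcome, the Data and Knowledge Management Center reconciles every participant's recorded arm with the central table by FC, sex and age stratum and recruitment order, and reports mismatches per FC. The report should note any households or clinics assigned together. D.8 should state whether closed envelopes were used throughout.
2. **D.12.** Stratify the primary log-rank test and the Cox model by the randomisation factors (FC, sex, age below 70 or 70 and over) unconditionally. This matches the analysis to the design. It does not remove selection within a centre, which is why items 1 and 3 are needed.
3. **D.12.** Keep intention to treat as primary. Pre-specify, before unblinded analysis, a sensitivity analysis that excludes any FC or block of participants whose assignments departed from the table, with cluster-robust variance if households or clinics were assigned together. Exclusions chosen after seeing results would carry little weight.

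**Cost.** A list-to-list comparison using tables that the Coordinating Unit produced, plus one extra analysis. With 11 FCs there are 44 strata and, at 11% events among 7,350 x 0.9 followed, about 728/44 = 16.5 events per stratum, so stratifying should cost little. The sensitivity analysis loses some precision, but one excluded centre of 1,000 still leaves about 1,905 per arm against the 1,877 required.
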